## Abstract

**Background:**

Recurrent implantation failure (RIF) in the majority of patients undergoing in vitro fertilization and embryo transfer (IVF-ET) is caused by various factors such as maternal age, embryo quality, endometrial receptivity (ER), and immunity. The incidence of RIF is usually between 5 and 10%. Previous studies have shown that herb-partitioned moxibustion on the navel is one of the treatment methods of acupuncture with a positive effect on pregnancy. However, its application in the treatment of RIF has not been reported. Therefore, this study aims to evaluate the effectiveness and safeness of herb-partitioned moxibustion on the navel in improving the outcome of frozen embryo transfer (FET) in patients with RIF.

**Methods:**

This study conducts a randomized controlled trial (RCT). It is planned to recruit 210 patients undergoing RIF for FET from Affiliated Hospital of Shandong University of Traditional Chinese Medicine and randomly divide them into the treatment group and the control group in a ratio of 1:1. The patient of the treatment group will be treated with herb-partitioned moxibustion on the navel once a week for three consecutive menstrual cycles. No intervention will be used in the control group for 3 menstrual cycles. In the fourth menstrual cycle, all patients will undergo artificial cycle to prepare the endometrium for FET. The pregnancy outcomes will be recorded after a 3-month follow-up. Primary outcome will be assessed as the ongoing pregnancy rate compared with the control group. Secondary outcomes include the endometrial type, resistance index (RI), pulsatility index (PI) of the bilateral uterine artery, endometrial blood flow, serum estradiol (E_2_), progesterone (P), biochemical pregnancy rate, implantation rate, and clinical pregnancy rate.

**Discussion:**

If the results show that the herb-partitioned moxibustion on the navel can improve IVF-ET outcomes in patients with RIF, it will be recommended in clinical practice.

**Trial registration:**

Chinese Clinical Trial Registry (ChiCTR) ChiCTR2100043954. Registered on 8 July 2021.

**Supplementary Information:**

The online version contains supplementary material available at 10.1186/s13063-022-06156-5.

## Introduction

### Background and rationale

Since the birth of the first test-tube baby in 1978, the technology of IVF-ET has been continuously innovated and developed. This innovation has made significant improvements in conception rate, implantation rate, and live birth rate. However, due to factors such as maternal age [1, 2], embryo quality [3], ER [4, 5], and immunity [6, 7], some patients who have received high-quality embryo transfers had unsuccessful pregnancy whereas more than 50% of the patients ended up with implant failure or biochemical abortion [8]. By definition, RIF is when women under the age of 40 years fail to achieve a clinical pregnancy after transplantation of at least four high-quality embryos in at least three fresh or frozen cycles [9, 10]. It has been reported that the incidence of RIF in IVF-ET patients may reach 5–10% [11], so RIF has become an issue of concern in current reproductive research.

In Western medicine, the main treatments for RIF are surgery and drugs. Surgical treatment includes hysteroscopic operation before transplantation to stimulate endometrial repair and growth by scraping the endometrium [12–14]. On the other hand, drug treatment mainly includes human chorionic gonadotropin [15], growth hormone [16], glucocorticoid [17], and oral letrozole [18]. Western medicine is adopted when RIF is combined with other diseases, due to the lack of effective treatment measures for RIF alone [19]. As a characteristic and representative way of traditional medicine, acupuncture has a comprehensive treatment effect of multiple channels, multiple links, and multiple targets. It treats systemic diseases with specific operation methods and conduction of meridians and acupoints. It has the characteristic that “internal disease is treated by external intervention” [20]. Therefore, it has been gradually accepted by domestic and foreign experts in the field of reproduction and is also applied in the prevention and treatment of RIF. The results have suggested that acupuncture has a significant effect on improving the implantation rate and clinical pregnancy rate in patients undergoing RIF [21, 22]. Herb-partitioned moxibustion on the navel belongs to the category of acupuncture. This method uses the Shenque acupoint (CV8) as the operating position. It puts medicinal powder in Shenque acupoint and cooperates with moxibustion to stimulate meridian qi. Further, it dredges meridian-collaterals, regulates qi-blood and functions of internal organs, and prevents and cures diseases. The structure of the Shenque acupoint is the most special among all acupuncture points. According to a previous study [23], it has been confirmed that it has a clear vascular structure from the perspective of vascular biology. Moxibustion can directly act on the intima and promote its microcirculation, which is the basis of Shenque treatment effect specificity. In addition, it has been found that in infertility patients with hypoluteal function, herb-partitioned moxibustion on the navel can effectively reduce RI and PI, and then improve the intrauterine blood perfusion, increase the endometrial thickness, and ultimately improve the pregnancy rate [24]. Another study [25] have found that herb-partitioned moxibustion on the navel can improve the quality of oocytes in elderly infertile patients by regulating the retinol metabolism pathway and glycerophospholipid metabolism pathway. However, there are no cases of herb-partitioned moxibustion on the navel for the treatment of RIF. Therefore, this study intended to use an RCT to observe the therapeutic effect of herb-partitioned moxibustion on the navel for RIF and explore its mechanism. In conclusion, Fig. 1 summarizes the preceding background to the study flowchart.

**Fig. 1 Fig1:**
[figure not shown]
Research background flowchart

## Methods

### Study objective

This study aims to investigate the effect of herb-partitioned moxibustion on the navel on the improvement of the outcomes of FET in patients with RIF.

### Trial design and setting

This is an RCT study. Participants will be recruited from the Affiliated Hospital of Shandong University of Traditional Chinese Medicine. Eligible participants will be randomly divided into the treatment (herb-partitioned moxibustion on the navel) or control group at a ratio of 1:1. The study flow chart and schedule are as shown in Fig. 2 and Table 1 (SPIRIT figure) respectively. The SPIRIT checklist is presented in Additional file 1. The main study sites will be the center of reproduction and genetics of Integrated Chinese and Western Medicine and the Center of Traditional Chinese Medicine External Treatment in the Affiliated Hospital of Shandong University of Traditional Chinese Medicine. This protocol follows the SPIRIT Reporting Guidelines [26].

**Fig. 2 Fig2:**
[figure not shown]
The study flowchart

**Table 1 Tab1:** Schedule of the study process (SPIRIT figure)

	Study period						
	Enrollment	Post allocation					
Timepoint	1st visit	1st MC	2nd MC	3rd MC	4th MC	14 days after FET	3 months after FET
**Enrollment:**							
Eligibility screen	√						
Informed consent	√						
Allocation	√						
**Interventions:**							
Herb-partitioned moxibustion on the navel		√	√	√			
Artificial cycle					√		
**Assessments:**							
Serum estrogen					√	√	√
Serum progesterone					√	√	√
Ultrasonography	√	√	√	√	√	√	√
Pregnancy test					√	√	
Pregnancy outcome					√	√	√
Telephone follow-up						√	√

### Eligibility criteria

#### Inclusion criteria

Patients who meet the following criteria will be enrolled in this study:

(1) Patients with RIF (comprising patients who fail to achieve a clinical pregnancy after transplantation of ≥ 4 high-quality embryos in ≥ 3 fresh or frozen cycles [11]) and (2) patients who have undergone in vitro fertilization through GnRH-antagonist protocol with the number of high-quality embryos ≥ 2.

#### Exclusion criteria

(1) Age > 40 years; (2) BMI ≥ 25 kg/m 2[27]; (3) the subjects had used any steroid drugs in the first 3 months; (4) patients who have been diagnosed with diseases affecting the uterine cavity, such as uterine malformation, endometriosis, and submucous fibroids; (5) patients or their partners having abnormal karyotypes (excluding chromosomal polymorphisms); (6) patients with recurrent pregnancy loss confirmed by ultrasound or histopathology as two or more clinical pregnancy failures; (7) patients who have been diagnosed with thin endometrium ( < 6 mm before embryo transfer); (8) previous history of radiation and chemotherapy; (9) allergic to umbilical medicine powder; (10) there are lesions around the umbilicus and it is not suitable for moxibustion; and (11) patients participating in other clinical trials during the proposed study.

### Dropout criteria

Patients who voluntarily withdraw or have poor clinical compliance during the observation period or are found not to meet the inclusion criteria after enrolment will be considered as having dropped out.

### Interventions

The treatments will be performed by a licensed acupuncturist who has at least 5 years of experience with acupuncture.

### Treatment group

Patients in the treatment group will be administered with herb-partitioned moxibustion on the navel once a week for three consecutive menstrual cycles. The artificial cycle will be used in endometrium preparation during the fourth menstrual cycle before embryo transfer.

The specific operations of herb-partitioned moxibustion on the navel are as follows [28]: (1) preparation powder of herb-partitioned moxibustion on the navel: Loranthus parasiticus, Semen cuscutae, Eucommia ulmoides, Cinnamon, Peach kernel, Red peony root, Angelica sinensis, Ligusticum chuanxiong, Rhizoma cyperi, and Borneol will be mixed in a certain proportion and crushed through the micro sifter and stored them in a dark tank for later use. (2) To prepare a dough ring: Make the flour into a ring with warm boiling water for later use. The inner diameter of the ring is about 3 cm, the outer diameter is about 6 cm, the inner wall height is about 2 cm, and the outer wall height is about 3 cm. The middle hole is the same size as the patient's umbilical hole. (3) Preparation of moxa cone: Moxa is squeezed into a cone-shaped body (about 1 cm in diameter and 1 cm in height) with a flat bottom and a tip and it is required to be twisted tightly and set aside. (4) Operation: The patients are placed in the supine position, and the dough ring is placed over the navel after routine disinfection of the umbilicus with 75% ethanol, the middle hole of the dough ring corresponding to the navel, and then take the powder of herb (about 8–10 g) and fill the belly button with moderate tension. Then, put the moxa cone over the powder, and add a new one after burning it out naturally. The procedure will take approximately 2 h and approximately 10 moxa cones will be used. Patients will be asked to close their eyes and rest during the procedure. After moxibustion, the umbilicus will be affixed and sealed with a medical applicator and take it off after 24 h. The operation process of the herb-partitioned moxibustion is presented in Fig. 3.

**Fig. 3 Fig3:**
[figure not shown]
The operation process of the herb-partitioned moxibustion on the navel

For the artificial cycle operation, oral estradiol valerate 4–6 mg will be given once a day starting from the fourth menstrual cycle day 3 to 5 of the fourth menstrual cycle. When the thickness of the endometrium is > 7 mm on vaginal B ultrasound, patients will be administered with dydrogesterone (10 mg three times per day, orally) and progestin (40 mg daily, intramuscularly). FET will then be performed 3 days after administration of dydrogesterone and progestin. Progesterone will be administered after FET for sustained luteal support until 10 weeks after gestation. But when the endometrial thickness exceeds 15 mm, the FET will be canceled.

### Control group

No intervention will be administered to the control group during the 3 menstrual cycles. However, an artificial cycle will be performed during the fourth menstrual cycle to prepare the endometrium before embryo transfer.

### Adherence

A coordinator in the research center will be in charge of the case report form (CRF) to ensure that data for each participant is accurately recorded. Several methods will be used to explore patient treatment compliance, including frequency of administration of herb-partitioned moxibustion on the navel and weekly telephone follow-up to ensure the findings are valid and reliable. Patients who failed to receive timely treatment on the same day will be identified and their data recorded.

### Concomitant care

Participants will not be allowed to take other Chinese herbal supplements or nutritional supplements to enhance ER for 3 months prior to enrollment into the study as other supplements may affect the herb-partitioned moxibustion applied on the navel.

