#### Retention

The research assistant will conduct weekly follow-ups to remind the participants of upcoming doctor/data collection appointments after enrollment and will record any adverse effects of the herb-partitioned moxibustion on the navel.

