#### Randomization and allocation

Participants will be randomly allocated into treatment or control groups at a rate of 1:1 by a computer-generated randomization sequence generated by the data coordinating center with SAS software version 9.2 (SAS Institute, Cary, NC). Allocation will be made by a designated researcher who will have no contact with any participant and will not be involved in the collection and analysis of the data. Due to the nature of the intervention, it will not be feasible to conceal the allocation from the practitioner and participants. The practitioner will not be allowed to disclose any information concerning their treatment to the participants or the assessor.

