#### Protocol amendments

Any modification of the protocol may affect the progress of the clinical study and the potential benefits to participants. If the study objective, study design, patient population, sample size, or study procedure change, the formal revision of the protocol is required. Any amendments to the protocol will be approved by the DMC and submitted to the relevant ethical review bodies.

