## Discussion

This is an RCT to evaluate whether the herb-partitioned moxibustion on the navel improves FET outcomes in RIF patients. A total of 210 participants from the Center for External Treatment of Traditional Chinese Medicine and the Reproductive Genetics Center of Integrated Traditional Chinese and Western Medicine in the Affiliated Hospital of Shandong University of Traditional Chinese Medicine will be recruited from March 2021. The results of this study will provide effective evidence that the herb-partitioned moxibustion on the navel improves the pregnancy outcome of women with RIF.

Herb-partitioned moxibustion is a treatment method comprising acupuncture and moxibustion. It exerts combined therapeutic effects of Chinese medicine and moxibustion through Shenque point. The selected traditional Chinese medicines of the herb-partitioned moxibustion on the navel are Loranthus parasiticus, Semen cuscutae, Eucommia ulmoides, Cinnamon, Peach kernel, Red peony root, Angelica sinensis, Ligusticum chuanxiong, Rhizoma cyperi, and Borneol, whose main functions are to tonify the liver and kidney, warm Yang, and promote qi as well as promote blood circulation and remove blood stasis. Related studies [31, 32] found that the endometrial basilar artery RI of patients with RIF decreased after the intervention of Chinese medicine and vaginal ultrasound showed that the echo of the endometrial-myometrial interface (EMI) area was improved and the difference was statistically significant (*P* < 0.05). It showed that Chinese medicines can increase the uterine blood flow perfusion and is helpful to improve patients with ER and early pregnancy outcome. In addition, other studies have confirmed that moxibustion can increase the thickness of the endometrium, improve the blood perfusion in the uterus, and then improve the ER and increase the chance of conception [24, 33]. However, there has been no study on the evaluation of the effects of the herb-partitioned moxibustion on the navel on the outcome of pregnancy in RIF patients. Therefore, the proposed study will administer herb-partitioned moxibustion on the navel of RIF patients to explore the effect on FET outcome.

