## Trial status

The trial was registered at the ChiCTR. This trial is at version 1.5, 8 July 2021 (ChiCTR). The actual study start date was 20 October 2021 and the anticipated study end date is 30 June 2022. The first patient was recruited on July 15, 2021; the anticipated recruitment end date is 31 December 2021.

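### The ban on other Chinese herbs and receptivity supplements ends at enrolment, before the moxibustion cycles it is meant to protect, so co-treatment that differs by arm could bias the ongoing-pregnancy comparison

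*Protocol article*

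**What the plan says.** The one rule on co-treatment with herbs or supplements is in the Concomitant care section of the protocol article. It bars other Chinese herbs and continues: "or nutritional supplements to enhance ER for 3 months prior to enrollment into the study as other supplements may affect the herb-partitioned moxibustion" (ER is endometrial receptivity).

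The sections that bear on it are these:

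- **Treatment group:** women are "administered with herb-partitioned moxibustion on the navel once a week for three consecutive menstrual cycles". Table 1 places moxibustion in the first three cycles after allocation and the artificial cycle in the fourth.
- **Control group:** "No intervention will be administered to the control group during the 3 menstrual cycles". There is no sham.
- **Randomization and allocation:** "it will not be feasible to conceal the allocation from the practitioner and participants".
- **Discussion:** the protocol's own view is that "Chinese medicines can increase the uterine blood flow perfusion and is helpful to improve patients with ER and early pregnancy outcome".
- **Primary outcomes:** ongoing pregnancy, judged by fetal heartbeat after 12 weeks of gestation.

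**The concern.** A rule under the heading of concomitant care, justified by possible interference with moxibustion, should cover the time when moxibustion is given. This one stops at enrolment. Read as written, a woman may start other Chinese herbs or receptivity supplements the day after she is randomised.

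In many trials equal background use could be assumed. Here that is less safe. The women have had repeated failed transfers, are cared for at a traditional Chinese medicine hospital, and know their allocation. Controls are offered nothing for three cycles and might seek something themselves. Treated women, in weekly contact with an acupuncturist, might equally be drawn to add herbs. Randomisation balances the arms at entry but does not prevent care from diverging afterwards. More use among controls would dilute a true effect, and more use among treated women would add to the apparent effect.

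**Working it through.** **1. Does any other section close the gap?**

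| Section | What it covers | Extends the ban past enrolment? |
|---|---|---|
| Exclusion criteria | Earlier steroid use; joining other trials during the study | No; self-chosen herbs and supplements are not covered |
| Control group (and Methods in the Abstract) | What the trial gives controls | No; silent on what they take themselves |
| Adherence | Moxibustion frequency, weekly telephone follow-up | No mention of co-treatment |
| Retention | Weekly reminders and adverse effects | No mention of co-treatment |

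**2. How long is the uncovered period?** Taking 28-day cycles, and assuming 10 to 14 days of estradiol (the document fixes its start at cycle day 3 to 5 and transfer 3 days after progestin starts, but not its length):

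- three cycles: 3 × 28 = 84 days
- transfer: 84 + 4 + (10 to 14) + 3 = day 101 to 105
- 3 months after transfer: + 90 = day 191 to 195

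With 35-day cycles the first term is 105 and the end falls on day 212 to 216. The stated window covers none of these days. The part with moxibustion is about 84 days (105 with 35-day cycles).

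**3. The plan's sample size.** The plan gives 94 per arm for 80% power, a two-sided pooled Z test at 0.05 and an effect of 20%, read here as an absolute difference. The control rate is not stated, so 94 cannot be confirmed. With a 20-point difference, the formula gives 93 at 30% versus 50%, 94 at a control rate of about 30.5% to 31%, and 82 at 20% versus 40%. The inflation for loss reproduces: 94 / (1 − 0.10) = 104.4, rounded up to 105 per arm and 210 in total. I therefore take 30% versus 50% as the base case.

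**4. Illustration of what differential use could do.** The control rate, the uptake and the benefit of the co-treatment are assumptions, not figures from the document. Uptake is set at 30%. The benefit is set at 10 points (half the target effect) or 20 points (all of it), so an arm with users shifts by 0.30 × 0.10 = 0.03 or 0.30 × 0.20 = 0.06.

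With n = 94 per arm, d = p₁ − p₀ and p̄ = (p₁ + p₀)/2:

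- SE₀ = √[2p̄(1 − p̄)/n]
- SE₁ = √{[p₀(1 − p₀) + p₁(1 − p₁)]/n}
- power = Φ[(d − 1.96·SE₀)/SE₁]

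Base case, 0.30 versus 0.50: SE₀ = 0.0715, SE₁ = 0.0700, (0.20 − 1.96 × 0.0715)/0.0700 = 0.857, so power is 0.804.

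| Scenario | Benefit | Control vs treated | Chance of a significant result |
|---|---|---|---|
| No co-treatment | none | 0.30 vs 0.50 | 0.804 |
| Controls only | 10 points | 0.33 vs 0.50 | 0.660 |
| Controls only | 20 points | 0.36 vs 0.50 | 0.491 |
| Both arms equally | 10 points | 0.33 vs 0.53 | 0.796 |
| Both arms equally | 20 points | 0.36 vs 0.56 | 0.790 |
| Treated only, moxibustion inert | 10 points | 0.30 vs 0.33 | 0.073 |
| Treated only, moxibustion inert | 20 points | 0.30 vs 0.36 | 0.141 |

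The last two rows count rejection in either direction, against a nominal 0.05.

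Changing the assumed control rate leaves the pattern intact. For use by controls only with a 10-point benefit, power falls from 0.855 to 0.712 at a 20% control rate and from 0.788 to 0.647 at 40%.

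**The case against.** The strongest reply is that this is a slip of wording. The heading, the word other and the stated reason all suggest that the authors meant an on-treatment ban. I agree that this is likely, but the text does not set one, and a rule has to be followed as it is written.

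A second reply is that a 3-month washout makes sense on its own, since residual effects of earlier herbs could alter the response to moxibustion. That is fair, and the washout should stay. It leaves concurrent use uncovered, to which the reason applies at least as strongly.

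A third is that a journal article condenses the full protocol. That would excuse silence on case report form fields or a list of prohibited products. It does not excuse a section on this very topic that states a window ending at enrolment. If the full protocol has an on-treatment ban, the published sentence misreports it.

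A fourth is that the stated reason reaches only the three moxibustion cycles, so a ban through the transfer cycle and early pregnancy goes too far. The reason given in Concomitant care does stop there. The Discussion, however, credits Chinese medicines with an effect on early pregnancy outcome itself, and that supports running the ban to the primary outcome.

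Last, the sizes above are hypothetical. This stands. The document gives no uptake figure, no pregnancy-rate effect for supplements and no evidence that use would differ by arm. The larger shifts need 30% use in one arm and none in the other, with a supplement as effective as the full 20-point target.

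**Conclusion.** The concern holds. The window is badly fixed: it ends before the treatment that the rule is meant to protect. In an unblinded trial with an untreated control arm, it leaves open a co-treatment that the protocol itself believes helps the outcome.

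The consequence is a possibility, not a demonstrated bias. Only use that differs by arm matters, and its direction and size are unknown. Under the stated assumptions, power could fall from 80% to between 49% and 66%, or the false-positive rate could rise from 5% to between 7% and 14%, while equal use leaves power at 79% to 80%. The randomised intention-to-treat comparison remains valid for moxibustion against no moxibustion under the care actually received. What weakens is the attribution of a difference, or of its absence, to moxibustion. This should be fixed, but it does not invalidate the trial.

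**What to change.** Reword the Concomitant care sentence so that the restriction on other Chinese herbal and receptivity-enhancing supplements runs from 3 months before enrolment through the primary-outcome assessment, identically in both arms. Ask about any use at the contacts already planned under Adherence and Retention ("The research assistant will conduct weekly follow-ups to remind the participants of upcoming doctor/data collection appointments after enrollment") and record product and dates. Keep users in the intention-to-treat analysis and report use by arm.

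The cost is one sentence, one added question and a formal amendment: "Any amendments to the protocol will be approved by the DMC and submitted to the relevant ethical review bodies". The longer restriction asks more of participants and might slightly lower willingness to enrol. It also comes after recruitment has begun: "The first patient was recruited on July 15, 2021; the anticipated recruitment end date is 31 December 2021". Women who started under the current wording should be asked about their use retrospectively and reported separately. Recording use is worthwhile even where the ban cannot be extended, because without it the sponsor cannot show that co-treatment was balanced.
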